## Abstract

**Background:**

In the present investigation the study protocol and the results at baseline of a workplace intervention are reported. It is hypothesised that the reduction of the physical and psychosocial workload of healthcare workers increases 1 their self-assessed physical and mental work ability, and 2. clients’ satisfaction with care.

**Methods:**

Two-arm, cluster-randomised trial. Outcome data on workers and clients are collected in questionnaires at baseline, and two follow-ups between 2019 and 2021. Participants of the interventions are healthcare workers of 11 healthcare providers in Germany. At baseline, the intervention arm comprised 22 clusters (*n* = 174 workers); the control arm, 47 clusters (*n* = 276). The intervention consists of interviews and workshops, in which employees propose measures aiming to reduce the physical and psychosocial load, and strengthen resources at work. The primary outcome is the workers’ physical and mental work ability. The secondary outcome is the clients’ satisfaction with care.

**Results:**

There was no evidence of substantial differences between trial arms at baseline concerning the outcomes. The design effect estimates for physical and mental work ability were 1.29 and 1.05, respectively. At the end of the trial, effect sizes of at least 0.30 and 0.27 at the 80% power and 5% significance levels can be attained.

**Conclusions:**

The results suggest that the implementation of the study design has been satisfactory. The intervention is expected to provide evidence of relatively small to medium-size effects of the intervention activities on the work ability of healthcare workers and the clients’ satisfaction with care.

**Trial registration:**

Registration trial DRKS00021138 on the German Registry of Clinical Studies (DRKS), retrospectively registered on 25 March, 2020.

## Background

In Europe, nurses’ intention to give up their profession have been found to increase with the perception of higher job-related efforts, lower rewards at work, and stronger overcommitment to job demands [1]. Meta-analytic results have indicated that psychosocial factors involving high job demands and low job control are associated with prevalent and incident musculoskeletal symptoms involving neck, shoulder and back pain among hospital nurses and nursing aides [2]. In addition, the so-called effort-reward imbalance [3], i.e., the combination of high efforts and low rewards obtained from one’s work, has been related to larger odds ratios for the experience of burnout symptoms among nurses, particularly in Germany where higher levels of effort-reward imbalance at work have been reported [4]. A previous systematic review by Duhoux et al. (2017) on non-randomised workplace interventions aiming to promote the mental health of primary care nurses, revealed that burnout and job stress could be reduced by different types of person-centred interventions including cognitive behavioural and mindfulness techniques [5]. However, despite that organisational interventions are regarded as more effective strategies of health risk prevention, only one organisational intervention met the inclusion criteria in that systematic review. Furthermore, no randomised controlled interventions were included, even though the risk of bias in complex intervention studies can substantially be reduced by randomisation [6]. In the large meta-analysis by Ruotsalainen et al. (2015) on workplace interventions aiming to reduce the perceived job stress in healthcare workers, it was found that two organisational interventions comparing an intensive participatory programme for the improvement of working conditions to no intervention were not effective at reducing the workers’ job stress levels [7]. In addition, according to the results reported by Ruotsalainen et al. (2015) participative, randomised workplace interventions with a follow-up time of more than 12 months were also extremely scarce: From the 21 organisational interventions found by the authors, only the study of Uchiyama et al. (2013) was a cluster-randomised controlled participatory intervention [8], whose effects, however, were measured immediately after the six-month intervention and, consequently, are of limited validity. Thus, to the knowledge of the authors and the literature aforementioned, the effectiveness of participatory organisational interventions in healthcare workers at the workplace has been barely investigated within the methodological framework of randomised controlled trials.

Hence, the present study contributes to research by presenting the study protocol and baseline results of a cluster-randomised workplace intervention among healthcare workers: “HALTgeben” (“Higher Patient Satisfaction through Fair Working Conditions in Healthcare”). The study HALTgeben is an organisational workplace intervention with healthcare workers conducted in 11 German health services providers which aims to improve the work ability of workers, and, thereby, the satisfaction with care of hospital patients and individuals in elderly care (i.e. the clients). It is hypothesised that the reduction of physical and psychosocial workload of workers increases 1. their self-assessed physical and mental work ability, and 2. clients’ satisfaction with care. These hypotheses pertain the individual level (the self-assessment of work ability and clients’ satisfaction with care), and the cluster level as well (average workload of healthcare workers in the clusters). In the following sections, the study protocol and the results at baseline are reported according to the CONSORT Statement for cluster-randomised trials (see also the Supplementary material 2 for the corresponding check-list) [9].

## Methods

### Study design

The study is a two-arm, cluster-randomised intervention with healthcare workers conducted in seven general and three specialised hospitals, and an elderly care centre in Germany, whose wards constitute the clusters. A cluster-randomisation design was required due to the fact that it is an organisational workplace intervention whose main target are wards, and the randomisation of individuals is not feasible, since, in principle, the set of measures implemented in the intervention wards may affect all workers therein. A cluster-randomisation design helps reducing the risk of contamination effects between intervention and control wards and, at the same time, accounts for the correlations of individual measurements being observed within clusters. Outcome data are collected at baseline and at two follow-up times (T1 and T2) in surveys containing validated instruments. Data collection at baseline was performed before the interventions began in the intervention arm. The first follow-up measurement T1 in the single wards will be conducted successively no later than 6 weeks after the implementation of the first measures aiming to reduce the workload of healthcare workers. The final measurement T2 in all wards will be performed 12 months after the last T1 follow-up. Baseline data collection on workers and clients took place between June and December 2019. The follow-up measurements at T1 and T2 will take place in 2020 and 2021, respectively.

### Participants

#### Healthcare workers

Eligibility criteria of individuals to participate in the workers survey were being employed as a healthcare worker, being older than 18 years, and working most of the time in a single ward only. A census of the healthcare workers population was attempted, and, therefore, all eligible workers were contacted by mail and invited to participate in the surveys. Each contacted employee received a booklet with a brief description of the study, data privacy policies for the surveys, a registration sheet, and the corresponding consent form. Participants were asked to provide written informed consent prior to study enrolment and supply the name of the ward they usually work in. The information on wards was validated with internal lists provided by the hospitals and the elderly care centre. Hence, the clusters were defined based on the information supplied by the workers, the internal organisational structure and the type of health services provided in the healthcare organisations. Eligibility criterion for clusters was the unambiguous assignment to patient or elderly care, respectively. The enrolment of healthcare workers ended on 31 October, 2019.

#### Clients

The eligibility criteria for participation in the client surveys were being older than 18 years, being able to give informed consent to participation, being a responsive patient, and having sufficient skills in the German language. Clients (i.e. patients and individuals in elderly care in residencies and at home) are contacted in the participating healthcare organisations and receive a booklet with a brief description of the survey and data privacy information. All clients are required to consent explicitly to participate in the study before data collection. At baseline, T1 and T2 follow-up, approximately 600 patients and 150 individuals in elderly care will be surveyed successively in a cross-sectional design in the intervention and control wards. Participation in the client surveys is anonymous. The outcome data on clients are collected by interviewers either as self-administered questionnaires, or personal interviews upon clients’ request. The interviewers receive a three-hour training in survey methodology provided by the authors from Ulm University before data collection.

### The intervention

The intervention addresses healthcare workers only, and is performed by four consultants whose areas of expertise cover work design and organisational development. Even though the interventions target whole wards in the intervention arm, data on workload and work ability is available only from employees consenting to participate in the worker surveys (i.e., not all workers in the single intervention wards take part in the surveys). The intervention is based on the concept of work ability [10, 11] and focuses on the balance between the individuals’ capacities and their work demands [12]. The main target of the intervention is to achieve that workers accomplish their work duties, by considering how individual characteristics and capacities of the individual workers may be aligned with the definition of work and task processes throughout different life phases. The consultants’ approach specifies four age-dependent main career stages: entrance, development and transition, continuity, and exit [12]. It is assumed that each career stage requires appropriate task and work specifications. The intervention is implemented in four phases (Fig. 1). Phase 1: The consultants ask the participating organisations for information regarding the organisation as a whole such as main work tasks of targeted employee groups, shift schedules, reports on occupational risk assessments, age structure, work council agreements, and work and operating instructions. Phase 2: Voluntary employees and supervisors in the intervention wards are interviewed and asked, among others, for their assessment on workplace aspects such as work organisation and processes, age-critical work tasks and workload, psychosocial demands, and degree of cooperation with colleagues of different ages. The interviews are conducted by means of a semi-structured questionnaire with an open-answer format. Phase 3: The consultants summarise the information provided by the organisations and the interviewed workers and supervisors according to the career stages mentioned above, and the five components of the work ability concept, namely, health capacity, occupational competence, attitudes and motivation, work organisation and management, and life-domain balance [11]. Afterwards, the interviewed workers are invited to participate in a workshop which lasts about 3 h. The consultants present and discuss the results in the workshop, and ask participants to propose measures aiming to enhance their work ability, improve their working conditions, and adapt the work environment to an ageing workforce. Phase 4: In each participating organisation so-called “initiatives circles” are implemented, in which the intervention measures proposed in the workshops are appraised regarding their feasibility. Members of the initiative circles may be managing board executives, managers of the healthcare departments, works council, and quality management or human resources representatives, who decide which measures can be implemented by the intervention wards themselves, and which require executive board approval. From a temporal perspective, the measures are categorised as short-term (e.g., ergonomic measures), medium-term (e.g., alignment of shift schedules according to workers’ needs in the different life phases), and long-term (e.g., personnel recruitment, work processes between departments or occupations). From a content perspective, the measures are categorised as individual (e.g., exercise programmes), inter-personal (e.g., health-promoting leadership) and structural (e.g., modification of work processes) [13].

**Fig. 1 Fig1:**
[figure not shown]
Schematic representation of the intervention phases

### Outcomes

The primary outcome is the self-assessed physical and mental work ability of employees. The secondary outcome is clients’ satisfaction with care. In addition, since the intervention effects are assumed to be the consequence of the reduction of the psychosocial load at work, the effort-reward imbalance of workers will be considered in additional analyses in order to evaluate a potential mechanism by which the intervention may have an effect on work ability [3]. These analyses will rely on theoretical considerations of the work ability concept in which the health status of individual workers is believed to be a determining antecedent of the appraisal of one’s own work ability [14]. All outcomes are measured by appropriate validated psychometric instruments freely available to scientists for research purposes. The questionnaires for healthcare workers comprise basic socio-demographic information, physical and psychosocial working conditions, work ability, and perceived physical and mental health (Table S1, Supplementary material 1). The questionnaires for clients include questions related to basic socio-demographic information, a set of scales measuring satisfaction with care, and a generic general health question (Tables S2 and S3, Supplementary material 1). Healthcare workers may fill out the questionnaires either online or as a paper-pencil version, and receive on request from the authors at Ulm University a short personalised report of their responses to the survey. The questionnaires for clients are available as a paper-pencil version only.

### Sample size

The sample size was calculated with the formulae provided by Dreyhaupt et al. (2017) [15], which considers the intraclass correlation coefficient (ICC), the average cluster size (m), the number of clusters (J), and the design effect (DE). The approach for calculating the sample size was to estimate the minimum effect attainable for a given sample and cluster size. An estimate of the ICC = 0.037 was taken from the intervention study of Mongini et al. (2012) conducted with a sample of Italian public servants [16]. Furthermore, it was assumed that a total of 50 clusters could be expected with an average cluster size of m = 5. Under these assumptions, a design effect DE = 1 + ICC*(m-1) = 1.33 was estimated, so that a total sample size of 500 participants was found to be required in order to detect a minimum effect of 0.30 at the 80% power and 5% significance levels. A total sample size of 500 individuals in a cluster-randomised design corresponds to an effective total sample size of 375 in a study with individual randomisation [15].

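### Sample size: the printed cluster size of 5 does not give the printed design effect of 1.33, total of 500 or effective size of 375; a cluster size of 10 gives all three

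*Protocol article*

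**What the plan says.** All the relevant statements are in the protocol article, Methods, Sample size.

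- ICC: "An estimate of the ICC = 0.037 was taken from the intervention study", in a sample of public servants.
- Clusters: "it was assumed that a total of 50 clusters could be expected with an average cluster size of m = 5".
- Design effect, presented as following from these inputs: "a design effect DE = 1 + ICC*(m-1) = 1.33 was estimated".
- Total and target effect: "a total sample size of 500 participants was found to be required in order to detect a minimum effect of 0.30", at 80% power and a 5% significance level.
- Effective size: the section closes by equating the 500 with 375 individually randomised participants.

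The section describes its approach as deriving the smallest detectable effect from a given sample and cluster size. It states neither whether the test is one- or two-sided nor the allocation ratio.

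**The concern.** The section prints its inputs, its formula and its results, and presents the results as following from the inputs. They do not. The design effect, the total and the effective size each disagree with an average cluster size of 5.

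This is the only a-priori justification of the trial's size in the article. A cluster size of 5 and one of 10 describe different trials: 250 or 500 workers, with clearly different power for the target effect. The choice also decides how recruitment is judged. Results reports a realised average of 6.53 workers per cluster, which is 31% above a plan of 5 (6.53/5 = 1.31) but 35% below a plan of 10 (6.53/10 = 0.65). The Conclusions call the implementation of the design satisfactory so far. For cluster size, a reader cannot test that against a plan whose key input contradicts its own results.

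**Working it through.** **Inputs from the Sample size section:** ICC = 0.037; J = 50 clusters in total; m = 5; stated DE = 1.33, N = 500, N_eff = 375; effect 0.30; power 80%; significance level 5%.

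**Assumptions, because the section does not state them:** two-sided test, 1:1 allocation, standardised effect.

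**Formulae:** DE = 1 + ICC × (m − 1); N = J × m; N_eff = N/DE; detectable effect = (1.960 + 0.842) × √(4/N_eff) = 2 × 2.8016/√N_eff.

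**Step 1. The plan's figures from its own inputs (m = 5).**
- DE = 1 + 0.037 × 4 = 1.148, against 1.33.
- N = 50 × 5 = 250, against 500.
- If N = 500 is kept, N_eff = 500/1.148 = 436, against 375.

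None of the three is reproduced. Sidedness, power and allocation ratio do not enter these formulae, so no choice of them can help.

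**Step 2. Which change of input restores the printed figures?**
- 50 clusters per arm instead of in total: N = 100 × 5 = 500, but DE stays at 1.148 and N_eff at 436. Only one of the three is restored.
- A different ICC at m = 5: DE = 1.33 needs ICC = 0.33/4 = 0.0825, more than twice the stated value, and 50 × 5 is still 250.
- A different m at ICC = 0.037: DE = 1.33 needs m = 1 + 0.33/0.037 = 9.92. With m = 10, DE = 1 + 0.037 × 9 = 1.333, N = 50 × 10 = 500 and N_eff = 500/1.333 = 375. All three are restored.

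**Step 3. What each reading implies for the effect (two-sided, 1:1).**

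| | m = 5, J = 50 | m = 10, J = 50 |
|---|---|---|
| DE | 1.148 | 1.333 |
| N | 250 | 500 |
| N_eff | 218 | 375 |
| Detectable effect at 80% power | 2 × 2.8016/√217.8 = 0.380 | 2 × 2.8016/√375.1 = 0.289 |
| Power for 0.30 | 60% | 83% |

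**Step 4. Sensitivity to allocation at N_eff = 375.** With shares p and 1 − p, the detectable effect is 2.8016/√(N_eff × p × (1 − p)). At the baseline split of 174:276 given in the Abstract, it is 2.8016/√(375 × 0.387 × 0.613) = 0.297. At 1:2 it is 0.307.

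**Step 5. Check of the assumptions against Results.** The effective sizes reported there are 345 and 423. At 1:1 and two-sided they give 2 × 2.8016/√345 = 0.302 and 2 × 2.8016/√423 = 0.272. The article states 0.30 and 0.27, so these assumptions match its own practice.

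**The case against.** The strongest reply is that this is one misprinted number. The design effect, total and effective size agree with one another, and only the printed m is out of line. If 10 was used, the calculation was sound. The article's current power claims, in the Abstract, Results and Discussion, rest on the realised cluster size and the ICCs estimated at baseline, not on this section. Enrolment of workers ended in October 2019, so no recruitment decision now depends on it.

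Most of this stands, and it limits the consequence. It does not remove the contradiction: the article nowhere says that 10 was meant, and a reader who applies the printed formula gets a different answer.

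Two stronger readings are tempting, and the document supports neither.

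- A reader might infer that the trial was planned to detect only 0.38. That figure holds only if m = 5 was really the planning value, which is the less likely branch.
- A reader might infer that 0.30 fails even at m = 10, because at 1:1 about 465 workers would be enough (4 × 2.8016²/0.30² = 349; 349 × 1.333 = 465) and 500 gives 0.289. This rests on an allocation ratio and sidedness that the section does not state. Under unequal allocation the figure is 0.297 or 0.307. The section also derives the effect from a given sample, so reporting 0.289 as 0.30 is ordinary conservative rounding. At most, calling 500 the required number is loose wording.

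**Conclusion.** The point holds as an internal contradiction in the a-priori sample size justification. The stated inputs give a design effect of 1.15 instead of 1.33 and 250 workers instead of 500; 500 workers at that design effect would have an effective size of 436 instead of 375. This part needs no assumption beyond the article's own formula.

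The likeliest explanation is that m = 10 was used and 5 was printed, because changing that one input restores all three outputs. On that reading the stated 0.30 is sound. If m = 5 was really planned with 50 clusters, the detectable effect is about 0.38 and power for 0.30 about 60%. These effect and power figures assume a two-sided 5% test, 1:1 allocation and, for the detectable effect, 80% power. Only the authors can say which reading is right.

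The realised power figures in Results do not inherit the error. This is a necessary correction to the record of the plan, not a threat to the trial's present power statement.

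**What to change.** Rewrite the Sample size paragraph around the cluster size actually assumed, and declare the sidedness and allocation ratio. With a two-sided 5% test, 80% power and 1:1 allocation:

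- **If m = 10 was assumed:** 50 clusters, DE = 1.33, N = 500, N_eff = 375, detectable effect about 0.29 (about 0.30 at the 174:276 split). The stated 0.30 can stay.
- **If m = 5 was assumed:** 50 clusters, DE = 1.15, N = 250, N_eff = 218, detectable effect about 0.38. The claims of 500 workers and 0.30 must then be withdrawn or justified separately.

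Add one sentence saying that the achieved average cluster size was 6.53, with more clusters than the 50 planned, and that the power figures in Results were computed from realised values and are unchanged.

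The cost is one corrected paragraph. No sample size, analysis or conduct of the trial changes.

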### Randomisation and implementation

Healthcare workers registered for the surveys by filling out a registration form addressed to Ulm University including personal information and the name of the ward they usually work in. Wards were then aggregated by the authors at Ulm University in clusters as described above, and stratified by hospital and elderly care ward. A list containing hospitals, clusters and number of registered participants was provided by the first author to the Institute of Epidemiology and Medical Biometry at Ulm University which generated the random allocation sequence and assigned clusters to interventions for the hospitals, independently from the authors at Ulm University and the consultants providing the intervention. The randomisation of clusters in the hospitals was performed in two steps with the statistical environment R. In the first step, the probability of being assigned to the intervention group was proportional to cluster size in each hospital, and a total of 10 clusters (i.e., one intervention cluster per hospital) were allocated to the intervention arm. Given the large variation of cluster sizes (Fig. 2), a sampling schedule proportional to size was required in the first step in order to ensure the generalisability of results by including the largest clusters in the hospitals, and to counter the expected power loss due to cluster and individual sample attrition in the subsequent follow-up measurements. In the second step, the random allocation proceeded by simple random sampling. However, given that only four consultants provide the intervention, a 1:1 allocation scheme for the remaining clusters was not feasible due to personnel limitations. Thus, the number of additional clusters in the intervention group in the hospitals was limited to 10. On the other hand, since the elderly care centre comprises only four wards, a simple random allocation in proportion 1:1 was performed in that case by the first author at Ulm University.

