### Statistical methods

The intervention effects on employees’ work ability and clients’ satisfaction with care will be estimated by means of generalised linear mixed-effect (GLM) regression models [17] with two levels of nesting (clusters within healthcare organisations). The GLM models are appropriate for cluster-randomised trials, since they account for the clustered structure of data in a longitudinal design [18]. Missing data at the end of the study will be handled by imputation routines and sensitivity analyses [19, 20]. The mean scores of the psychometric scales will be computed with available items if no more than 30% of the items defining the scale are missing [21]. The ICC at baseline are estimated from the variance components of a random-intercept model with two levels of nesting (clusters within organisations). The baseline data are analysed with a series of GLM Bayesian regression models (also called hierarchical models) by means of Markov Chain algorithms as described elsewhere [22]. The goodness-of-fit was assessed by the Deviance Information Criterion (DIC). Lower values of the DIC statistic indicate a better model fit [23]. Given the role of the effort-reward imbalance as a potential mediating mechanism between the intervention and the main outcomes (see methods section), the associations between physical and mental work ability with effort-reward imbalance and overcommitment are investigated in three regression models with the workers dataset. Due to the fact that health in the work ability concept is thought to be a determining antecedent of one’s own work ability perceptions, the fully adjusted models include two SF12-equivalent physical and mental health component scores [24]. In addition, for the patients dataset, the associations between the four indicators of satisfaction with care and the cluster-levels of psychosocial load of healthcare workers are estimated.

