## Discussion

The results at baseline suggest that the random allocation of clusters was satisfactory, since no substantial differences were observed between the intervention and control arm regarding the primary outcomes. According to the power analyses reported in the results section, one strength of the intervention is that effect sizes of at least 0.30 and 0.27 can be estimated at the 80% power and 5% significance levels, for physical and mental work ability of workers, respectively. Given that previous randomised organisational interventions have reported even larger effect sizes (standardised mean differences of − 1.23, − 0.55 and − 0.35) [7], the present study has sufficient power to detect substantial changes in the main outcomes.

A further strength of the study concerns the indication of an acceptable internal validity. Mainly successfully and widely tested questionnaires showing satisfying to good psychometric properties in previous studies [24, 31–35] and the present intervention as well (average Cronbach’s alpha over all instruments 0.74, see Supplementary material 1), were applied to measure independent (e.g., workload) and dependent variables (e.g., work ability, clients’ satisfaction). These measures allow comparisons of the present results with findings from other studies. Concerning the first study hypothesis, the results show associations of measures of effort-reward imbalance with work ability in workers. Hence, it is plausible to expect that a reduction of workload may result in increases of perceived work ability. In addition, the results indicate that these associations are mediated by perceived health (model 3 in Table 3). This mediation has been hypothesised previously, but has not been shown empirically so far [36]. However, the second hypothesis stating that the reduction of workload increases patients satisfaction did not receive support, since no cross-sectional associations were observed between workload and patients satisfaction (Table 4). Due to the low number of clusters in the elderly care centre, the second hypothesis cannot be investigated with the elderly care dataset.

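### Half of the hospital intervention clusters were assigned with probability proportional to size, and the analysis as described names no term for cluster size or assignment probability

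*Protocol article*

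**What the plan says.** **Allocation (Randomisation and implementation).** In step 1 in the hospitals, "the probability of being assigned to the intervention group was proportional to cluster size in each hospital". This draw placed one cluster from each hospital, 10 in all, in the intervention arm. Two reasons are given. One is "in order to ensure the generalisability of results by including the largest clusters in the hospitals"; the other is to offset power lost when clusters and workers drop out. For step 2: "In the second step, the random allocation proceeded by simple random sampling", and "the number of additional clusters in the intervention group in the hospitals was limited to 10". In the elderly care centre, "since the elderly care centre comprises only four wards, a simple random allocation in proportion 1:1 was performed". The list sent to the randomising institute held the hospital, the cluster and its number of registered participants. No other size measure is mentioned, so size is read here as registered workers.

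**Analysis (Statistical methods).** Effects are to be estimated by mixed models "with two levels of nesting (clusters within healthcare organisations" as levels. No fixed effects are listed for the final analysis. The baseline models in Tables 3 and 4 do list their covariates (personal characteristics, ward or organisation type, psychosocial and health scores), and cluster size is not among them.

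**Conclusion drawn (Discussion).** "The results at baseline suggest that the random allocation of clusters was satisfactory", because the arms did not differ substantially in the primary outcomes.

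**The concern.** Drawing units into a study with probability proportional to size can serve generalisability. Here every listed cluster is in the study anyway, and what the draw decides is which arm it joins. Favouring large clusters for one arm does not widen the population studied; it makes the arms differ in size. Under such a scheme the arms are comparable only given the stratum and the size used in the draw.

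Size counted as registered workers mixes ward size with willingness to take part, and only about 13% of workers responded. Either could be related to how work ability changes, how well measures are implemented, or who is lost. The article's own attrition rationale suggests that it expects larger clusters to withstand losses better, in which case loss to follow-up could differ between arms by design. A bias of this kind does not shrink as the sample grows, and random intercepts for cluster and organisation do not remove an association between treatment and size within a hospital.

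**Working it through.** **1. The plan's own figures.** Detectable effect = 2 × (1.96 + 0.84)/√N_eff. For N_eff = 345 this is 0.30, and for 423 it is 0.27, as stated in Results. From the Abstract, (174 + 276)/(22 + 47) = 450/69 = 6.52 workers per cluster, against 6.53 in Results. (Results also gives 67 clusters in total. The per-arm counts used here are the Abstract's and are taken as the workers registered at allocation.)

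**2. Size by arm.** Intervention 174/22 = 7.91; control 276/47 = 5.87. The difference is 2.04 workers; the ratio is 1.35.

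**3. How strongly assignment depends on size.** Assume 69 − 4 = 65 hospital clusters spread evenly over 10 hospitals, so 6.5 clusters and 6.52 × 6.5 = 42.4 workers per hospital. After step 1, 55 clusters remain for 10 places. For a cluster of size s, P(intervention) = s/42.4 + (1 − s/42.4) × 10/55.

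| Size s | Step 1 | Overall |
|---|---|---|
| 2 | 0.05 | 0.22 |
| 6.5 | 0.15 | 0.31 |
| 13 | 0.31 | 0.43 |
| 20 | 0.47 | 0.57 |

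Step 2 dilutes the dependence but does not remove it.

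**4. Is the observed gap what the scheme predicts?** The scheme was simulated 3,000 times with gamma-distributed sizes of mean 6.52. The coefficient of variation (CV) is an assumption, because the text gives none and the figure cited for size variation is not available here.

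| CV | Expected gap (workers) | Draws with a gap of at least 2.04 |
|---|---|---|
| 0.4 | 0.48 | 1% |
| 0.6 | 1.02 | 17% |
| 0.8 | 1.74 | 40% |
| 1.0 | 2.52 | 60% |

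Simple random draws in both steps give an expected gap of about 0 at every CV.

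**5. Cap on bias from a relation between size and level.** Bias = (slope, in outcome SD per SD of size) × (imbalance, in SD of size). Even if size explained all variation between clusters, the slope could not exceed √ICC: √0.05 = 0.22 (physical) and √0.01 = 0.10 (mental).

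At CV 0.8 the SD of size is 0.8 × 6.52 = 5.22. The imbalance is 1.74/5.22 = 0.33 SD for the expected gap and 2.04/5.22 = 0.39 SD for the observed gap. The caps are:
- physical: 0.22 × 0.33 = 0.07 to 0.22 × 0.39 = 0.09, so about 0.08 SD
- mental: 0.10 × 0.33 = 0.03 to 0.10 × 0.39 = 0.04, so about 0.04 SD

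Sensitivity to the CV, using the observed gap:
- CV 1.0: imbalance 2.04/6.52 = 0.31 SD; caps 0.07 and 0.03
- CV 0.6: imbalance 2.04/3.91 = 0.52 SD; caps about 0.12 and 0.05

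**6. What the baseline comparison can show.** Baseline means are 3.10 vs 3.15 (physical) and 3.04 vs 3.05 (mental), intervention first. In Table 3, Model 1, the arm coefficient for physical work ability is −0.10 (SE 0.11; interval −0.32 to 0.10). With outcome SDs of 0.91 to 0.98, that interval is too wide to exclude a shift of 0.08 SD. It also says nothing about change or attrition.

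**The case against.** The strongest reply concerns the model. A reader might infer that the planned analysis contains random effects only and so excludes cluster size. The article does not say that. It gives the model class and nesting and lists no fixed effects at all, and a fuller plan may well include size. This stands: the point cannot be that size has been ruled out. It rests on what the article does state, namely the allocation rule, its rationale, the baseline models without a size term, and the conclusion drawn from outcome means.

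A second tempting reading is that the bias could exceed a third of the 0.30 target, for example 0.11 SD from a slope of 0.3 SD of outcome per SD of size. That slope needs size to explain 0.3² = 9% of outcome variance, while all clusters together account for 5% and 1% at baseline. The documents do not support it. Even the caps in the working assume that size explains the whole of the between-cluster variance, which is implausible.

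A third is that allocation as a whole went by size, or was not random. It did not: 12 of the 22 intervention clusters came from draws that ignored size, and the size-dependent draw was still random with computable probabilities.

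Two further points stand. The attrition reason is separate from the generalisability reason and is not refuted here; placing larger clusters in the smaller arm raises its share from 22/69 = 32% of clusters to 174/450 = 39% of workers. And baseline outcomes were collected before allocation, so a stable relation of size to level can largely be handled through the baseline value. What that does not handle is a relation of size to change, implementation or loss.

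**Conclusion.** The concern holds in limited form. Assignment in the hospitals depends on registered cluster size by design, the arms differ in the predicted direction (7.9 vs 5.9), and the analysis as described does not condition on size or assignment probability. For a relation between size and level of work ability, bias is capped at roughly 0.08 SD (physical) and 0.04 SD (mental), against detectable effects of 0.30 and 0.27. This rests on a size CV of 0.8, on evenly sized hospitals and on the reported baseline ICCs. A relation with change over time is not strictly bounded by those ICCs, and the documents give no slope for it, so no bias has been shown to exist.

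The generalisability rationale does not hold for treatment assignment. Similar baseline outcome means do not show that size-dependent allocation is harmless for change or attrition. This is an inexpensive improvement that should be made before follow-up analysis; it does not invalidate the trial.

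**What to change.** - In the worker model and the hospital-patient model, condition on organisation, which is the randomisation stratum, and on the registered cluster size used in the draw, for example as log size.
- As a sensitivity analysis, weight clusters by the inverse of the probability of the arm they received. Re-running the R allocation routine many times on the original list gives these probabilities for the hospitals.
- Do not fit a size term in the elderly care client dataset: allocation there was not by size, and four wards cannot support it.
- Report registered cluster size by arm.
- In Randomisation and implementation, drop generalisability as a reason for size-proportional treatment assignment; the attrition reason can stay.
- In the Discussion, limit the favourable judgement on allocation to the similarity of baseline outcome means.

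The allocation list already holds the variables needed. The cost is a few lines in the analysis plan and a small loss of cluster-level degrees of freedom: one for size, plus ten if the 11 organisations become fixed rather than random effects, out of 67 to 69 clusters.
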